## **4.7. STUDY CRITERIA**

### **4.7.1. Patient Inclusion Criteria**

For inclusion in this trial, all the following inclusion criteria must be fulfilled. No waivers to inclusion criteria will be permitted.

1. Voluntarily agree to participate and can provide informed consent or have a duly appointed health care proxy established which/who has the authority to consent on behalf of the patient
2.  $\geq 18$  years of age
3. Inpatient hospitalization
4. Evidence of SARS-CoV-2 infection with the diagnosis of moderate to severe ARDS per Berlin definition ([ARDS 2012](#)), no more than 2 weeks prior to study enrollment
5. Patients at high risk of intubation or intubated with mechanical ventilation
6. Female patients of childbearing potential must be willing to use highly effective contraception measures starting with the Screening visit through 90 days after last dose of study treatment. Male patients with a female partner(s) of childbearing potential must agree to use highly effective contraceptive measures throughout the trial starting with the Screening visit through 90 days after the last dose of study treatment is received. Males with pregnant partners must agree to use a condom; no additional method of contraception is required for the pregnant partner

Note: Abstinence is acceptable if this is the established and preferred contraception method for the patient

7. Patients, or study participant's duly appointed health care proxy with the authority to consent on behalf of the patient, must consent to placement of a central venous access line for the administration of agenT-797

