| Title of Study: A Phase 1/2 Study of agenT-797 to Treat Moderate to Severe Acute Respiratory Distress Syndrome Secondary to SARS-CoV-2 or Influenza                                                                                         |                                                                                                                                                                                                                                                                                                                                                                                                                                                                                                                                                                                                                                                                                                                                                                                                                                           |
| Study Centers: Approximately 5 centers in the United States and Brazil                                                                                                                                                                      |                                                                                                                                                                                                                                                                                                                                                                                                                                                                                                                                                                                                                                                                                                                                                                                                                                           |

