## 4. INVESTIGATIONAL PLAN

### 4.1. OVERALL STUDY DESIGN

This is a Phase 1/2 study to evaluate the safety and potential efficacy of agenT-797, an unmodified, allogeneic iNKT cell therapy, in patients with moderate to severe ARDS secondary to SARS-CoV-2 or influenza, either with intubation or at high risk to be intubated, as determined by the Berlin definition ([ARDS 2012](#)).

**Completed:** Part 1 will employ a standard 3+3 dose escalation design of agenT-797. All patients will receive a single infusion of agenT-797. Patients will also receive other treatments and supportive care per discretion of the Principal Investigator. Once the maximum tolerated dose (MTD) of agenT-797 has been cleared in Part 1, an Expansion Cohort will be opened. A Safety Monitoring Committee (SMC) will be established to assess safety and decide on escalation to

next cohort and expansion dose, as well as any protocol modification to include less severe cases.

**Part 2 (Expansion)** of the study will evaluate an additional cohort in up to 15 patients:

- Cohort 4 – patients with moderate to severe ARDS secondary to SARS-CoV-2 or influenza, according to Berlin definition, who are on mechanical intubation

The SMC will continue to review safety.

The number of patients in each cohort is presented in [Table 2](#).

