## 4.4. STAGGERED COHORT ENROLLMENT

Each cohort will have a minimum of 3 patients enrolled. agenT-797 (Cohort 1) will be administered in the first patient, and treatment will be administered to the next patient 7 days after the last patient was administered agenT-797. Cohort 2 will be administered 14 days after the last patient was dosed in Cohort 1 and will follow the staggered dosing in Cohort 1 (every 7 days/patient). If patients tolerate low dose (Cohort 1) and intermediate dose (Cohort 2) treatment with agenT-797, Cohort 3 may be enrolled after 14 days.

An additional cohort in up to 15 patients will be evaluated:

- Cohort 4 – patients with moderate to severe ARDS secondary to SARS-CoV-2 or influenza, according to Berlin definition, who are on mechanical intubation

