- j Pregnancy testing for women of child-bearing potential: serum test at Screening.
- k Cytokines/biomarkers: D1 – preinfusion, end of infusion, and at 2, 4, and 8 hours postinfusion agenT-797, and as feasible thereafter. Cytokines for analysis may include but are not limited to: epidermal growth factor, eotaxin, fibroblast growth factor-basic, granulocyte-colony stimulating factor, granulocyte-macrophage colony stimulating factor, hepatocyte growth factor, interferon-alpha, interferon-gamma, IL-1 beta, IL-1 alpha, IL-1RA, IL-2, IL-2R, IL-3, IL-4, IL-5, IL-6, IL-7, IL-8, IL-9, IL-10, IL-12 (p40/p70) IL-13, IL-15, IL-17A, IL-17F, IL-22, IP-10, monocyte chemoattractant protein-1, MIG, MIP-1 alpha, MIP-1 beta, Regulated upon Activation, Normal T Cell Expressed and Presumably Secreted, tumor necrosis factor-alpha, vascular endothelial growth factor, and matrix metalloproteinase-9.
- l To be obtained 5, 15, and 30 min, and 1, 2, and 4 hours postinfusion.
- m To be obtained 2 hours postinfusion.
- n To be obtained in intubated patients if clinically indicated using microlavage techniques when possible.
- o To be obtained in intubated patients when possible.
- p Evaluations including physical examination and procedures required for lung injury score evaluation (chest X-ray, PaO2/FiO2 ratio, positive end-expiratory pressure, compliance, mL/cm H2O) as needed, including daily or more often until recovery ([ARDS 2012](#)).
- q As needed.
- r SOFA score will be calculated using results of the following tests: PaO2, FiO2, platelet count, need for mechanical ventilation, Glasgow Coma score, bilirubin, mean arterial pressure or use of vasoactive medications, creatinine, and diagnosis of COVID-19 ([SOFA](#)).
- s Patients must be SARS-CoV-2 or influenza positive at diagnosis; refer to [Section 4.7.1](#).

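### Inclusion criterion 4 requires SARS-CoV-2 infection with no waivers, so the influenza-only patients included in the title, design, Cohort 4 and schedule footnote s cannot be enrolled

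*Combined protocol and SAP*

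**What the plan says.** **Population as described.** The study title in the Synopsis reads "A Phase 1/2 Study of agenT-797 to Treat Moderate to Severe Acute Respiratory Distress Syndrome Secondary to SARS-CoV-2 or Influenza". Protocol Section 4.1 describes patients with "moderate to severe ARDS secondary to SARS-CoV-2 or influenza, either with intubation or at high risk to be intubated". The Cohort 4 definition also names both viruses wherever it appears (Synopsis; protocol 4.1 and 4.4; SAP 3.1 and 3.4). Footnote s to the Schedule of Assessments (protocol Table 3, repeated in SAP Table 4) says "Patients must be SARS-CoV-2 or influenza positive at diagnosis" and sends the reader to protocol Section 4.7.1.

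**Population as admitted.** Section 4.7.1 opens with "For inclusion in this trial, all the following inclusion criteria must be fulfilled", followed by "No waivers to inclusion criteria will be permitted". Criterion 4 is "Evidence of SARS-CoV-2 infection with the diagnosis of moderate to severe ARDS per Berlin definition", dated to within 2 weeks of enrolment. The Synopsis copy is the same. Influenza appears in the eligibility lists only in exclusion 8c, which permits patients with both SARS-CoV-2 and influenza.

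**Ventilation status.** Criterion 5 is "Patients at high risk of intubation or intubated with mechanical ventilation". Cohort 4 is limited to patients with moderate to severe ARDS "according to Berlin definition, who are on mechanical intubation". Part 1 is marked as completed.

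**The concern.** Eligibility text decides who receives an allogeneic cell product, and here the protocol gives two incompatible answers for a patient with influenza and no SARS-CoV-2. Footnote s makes this more than a loosely worded title: it states the wider rule and cites Section 4.7.1 for it, but that section holds the narrower rule.

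Influenza is also carried through the rest of the plan. It has a background section (2.2) and shares the treatment rationale (2.4). It is named in the exception to the 30-day death stopping rule (4.5.3), the adverse event definition (8.1.1) and the causality assessment (8.1.7). A reader would expect some influenza-only patients in the data.

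There are two possible outcomes. If sites apply criterion 4, there are none. If sites apply the title or footnote s, they breach a criterion that allows no waiver. Different sites could also choose differently. With at most 15 patients in Cohort 4, a few such cases would change who the cohort represents, and the baseline summaries in SAP 4.6 and 4.7 do not name causative virus.

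**Working it through.** No formula applies. SAP 3.2 states that no sample size calculation was done, and the plan gives no figure to reproduce on this point. The check is to take each kind of patient and read it against criterion 4, criterion 5, exclusion 8 and the Cohort 4 definition.

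| Patient | Criterion 4 | Criterion 5 | Exclusion 8 | Cohort 4 definition | Result |
|---|---|---|---|---|---|
| SARS-CoV-2 only, intubated | met | met | not triggered | met | can enrol |
| Influenza only, intubated | **not met** | met | not triggered | met | **cannot enrol** |
| Both viruses, intubated | met | met | allowed by 8c | met | can enrol |
| SARS-CoV-2 only, high risk, not intubated | met | met | not triggered | **not met** | passes the list, fits no open cohort |

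**Row 2 is the contradiction.** This patient matches the title, Section 4.1, the Cohort 4 definition and footnote s, and fails on criterion 4 alone. Because all criteria are mandatory and there are no waivers, one failure is decisive. The number of influenza-only patients who can properly enter Cohort 4 is 0 of up to 15.

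**Row 3 sets the limit of the point.** Influenza patients are not barred as such. Those who also have SARS-CoV-2 meet criterion 4 and are expressly allowed. Exclusion 8c is an exception to an exclusion, so it cannot supply the missing inclusion for row 2.

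**Row 4 is a smaller matter.** Criterion 5 is study-wide and agrees with the study-wide sentence in Section 4.1. The Cohort 4 definition adds intubation on top of it. With Part 1 completed, the numbered list simply does not carry the ventilation condition of the one cohort still to be evaluated. Exclusion 10, labelled as applying after Amendment 7, shows that the lists were updated for a later stage of the study elsewhere.

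**What happens in the analysis if a row 2 patient is treated.** The Safety Analysis Set (SAP 4.5) takes in everyone who received agenT-797, and SAP 4.11.2 uses the same set for clinical activity. The patient therefore stays in those main summaries. SAP 4.4.2 adds robustness checks with and without data affected by major deviations, and leaves it to a separate deviation specification to say what counts as major.

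**The case against.** The strongest case on the other side does not dispute criterion 4; it disputes how much follows from it. No objective or endpoint is specific to influenza. The primary objective is safety and tolerability, and the virus-specific objectives are exploratory and name SARS-CoV-2. Section 2.3 says the product is being evaluated initially for SARS-CoV-2, and no formal comparison is planned. All of this stands. A reader might infer that the trial loses half of its question, but the documents do not support that: influenza widens the intended population and is not a separate analysis. A descriptive study still needs one defined population, so the contradiction remains.

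A reader might also infer that any influenza-only patient enrolled would be a major deviation and would drop out of the results. SAP 4.4.2 does not go that far. The classification sits in a specification that is not among the documents, and the Safety Analysis Set keeps every treated patient.

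Finally, a reader might infer that criterion 5 admits non-intubated patients to Cohort 4. It does not, because such a patient still fails the Cohort 4 definition, which is repeated in the Synopsis, the protocol body and the SAP. A Cohort 4 of mixed intubation status would arise only if sites ignored that definition.

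**Conclusion.** The point holds for influenza-only patients. Criterion 4, in both places where it stands, bars patients whom the title, Section 4.1, the Cohort 4 definition and footnote s include, and no other passage resolves the conflict. The text is wrong as written and has to be reconciled.

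Its size is 0 eligible influenza-only patients out of up to 15 in Cohort 4. That figure restates the rule and does not forecast a loss, since the documents give no expected number of influenza patients. If few or none would have presented, the practical effect is small; if sites enrolled some under footnote s, those patients may be classed as protocol deviations.

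The conclusion assumes that sites treat the numbered criteria as binding, as Section 4.7.1 tells them to. It takes no position on which population is the right one. The most likely explanation is that criterion 4 was left unedited when influenza was added, but that is an inference. The missing intubation condition is a matter of clarity only.

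**What to change.** 1. **Protocol, Synopsis and Section 4.7.1, criterion 4:** reconcile with the title, Sections 4.1 and 4.4 and footnote s, in whichever direction the sponsor intends. Either criterion 4 names SARS-CoV-2 and/or influenza, or influenza is removed from the population wherever else it is stated. In both cases footnote s and the section it cites must say the same thing, in protocol Table 3 and in SAP Table 4.
2. **SAP 4.7:** add causative virus (SARS-CoV-2, influenza, both) to the planned summary and by-subject listing of diagnosis and extent of disease.
3. **Minor clarification, criterion 5 in both places:** add a cross-reference to the Cohort 4 definition so that the list points to its mechanical intubation condition.

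The cost is a short protocol amendment, which needs IRB/IEC approval under Section 11.1, and a small SAP edit. Removing influenza would touch more passages than widening criterion 4, but both are text changes.

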### **4.7.2. Patient Exclusion Criteria**

For inclusion in the trial, patients must have none of the following exclusionary criteria. No waivers to exclusion criteria will be permitted:

1. Currently participating and receiving study therapy of an investigational agent that is not registered for any other indication
2. Life expectancy of  $< 1$  month
3. Clinically significant cardiomyopathy
4. Pre-existing respiratory disease, such as significant chronic obstructive pulmonary disease requiring home oxygen, hospitalization, or systemic steroid use during the past year.
5. "Significant" pulmonary hypertension as mean pulmonary artery pressure  $\geq 20$  mmHg and evidence of right ventricular dysfunction or enlargement

6. Receipt of vaccines containing live virus within 4 weeks prior to first dose of study treatment
7. Known hypersensitivity to donor-derived cell therapy or their preservation solution
8. Active systemic bacterial or fungal infection or viral co-infection with the exception of:
  - a. Patients with rhinoviral infection (common cold) are permitted to participate
  - b. Patients on treatment and/or ongoing improvement with minor common infections (e.g., urinary tract infection, minor skin infections) are permitted to participate
  - c. Patients with both SARS-CoV-2 and influenza (co-infection) are permitted to participate
9. Pregnant or lactating women
10. **After implementation of Amendment 7:** Presence of multiorgan dysfunction syndrome; no organ failure should be seen other than the organ of interest, which is the lung

#### **4.8. PATIENT WITHDRAWAL FROM STUDY**

Patients must be withdrawn from the study in the following situations:

- Severe noncompliance to this protocol as judged by the Investigator and/or Sponsor
- Pregnancy
- Withdrawal of consent
- Investigator discretion
- Sponsor decision

#### **4.9. END-OF-HOSPITALIZATION OR DEATH**

After the patient has received a single infusion of agenT-797, the EOH is defined as patient discharge from the hospital or death.

#### **4.10. 30-DAY AND SAFETY FOLLOW-UP**

The Safety Follow-up period will be 30 days, and the patient will be contacted by telephone 3 and 6 months after discharge regarding any SAEs and to confirm survival, as feasible. The first Safety Follow-up Visit will be at Day 30 ( $\pm 2$ ), or at EOH. If a patient is discharged at Day 30, 30-day Follow-up will be the same as EOH. Please refer to [Table 3](#).

#### **4.11. REPLACEMENT OF PATIENTS**

Patients are at any time free to withdraw from the study. Such patients will always be asked about the reason(s) and the presence of any AEs. AEs should be followed up as outlined in [Section 8.1.5](#). The Investigator may also elect to discontinue patients from the study, for example, to pursue a different treatment option. Reason(s) for discontinuation will be documented.

Patients who are withdrawn from the study but have completed treatment (infusion of agenT-797), are to be considered evaluable for DLT, and will not be replaced. Any patient who is withdrawn and is not considered evaluable for safety during Dose Escalation will be replaced to ensure a minimum number of evaluable patients.

#### **4.12. ENROLLMENT STOPPING RULES**

Enrollment may be temporarily stopped if any of the following occur:

- A DLT (see [Section 8.1.4](#))
- Any toxicity that is unexpected, significant, and unacceptable (based on SMC review; [Section 8.2](#))
- Safety stopping rules ([Section 4.5.3](#))
- Documented Sponsor decision

#### **4.13. PREMATURE STOPPING OF STUDY**

The study may be prematurely stopped due to the following reasons:

- The discovery of an unexpected, significant, or unacceptable risk to the patients enrolled in the study
- A decision on the part of the Sponsor to suspend or discontinue the study
- Any other reason as determined by the Sponsor or SMC

The Sponsor will be responsible for all decisions pertaining to prematurely discontinuing the study.

#### **4.14. ASSIGNMENT OF PATIENT TRIAL NUMBER**

After a patient signs an ICF, the patient will be assigned a unique, sequential patient number. Once a number is assigned, it cannot be reassigned if the original patient is found to be ineligible or withdraws consent.

#### **4.15. TRIAL COMPLIANCE**

Compliance is ensured, as patients will be hospitalized ([Section 4.7.1](#)). Patients who are discharged (EOH) will be followed per [Section 4.5.7](#) and [Section 4.10](#).

#### **4.16. CLINICAL ASSESSMENTS AND PROCEDURES**

##### **4.16.1. Medical History**

Medical history will be taken during the Screening period ([Table 3](#)).

##### **4.16.2. Review of Screening Procedures**

Screening procedures will be conducted as outlined in [Table 3](#).

### **4.16.3. Review of Prior and Concomitant Medications**

#### **4.16.3.1. Prior Medications**

The following medications are not permitted:

- Receipt of vaccines containing live virus within 4 weeks prior to first dose of study treatment

#### **4.16.3.2. Concomitant Medications**

All medications are recorded from the date of ICF. Also see [Section 5.3.3](#) for prohibited concomitant medications.

### **4.16.4. Daily Assessments Throughout Hospitalization**

Disease evaluations will be recorded daily while patient is hospitalized. Additionally, selected evaluations at baseline (D1), + 24 hours (D2), + 72 hours (D4), + 5 days (D6), + 7 days (D8), + 10 days (D11), + 14 days (D15), + 21 days (D22), + 28 days (D29), D32 to EOH, and at other days if significant event(s) occur. The patient will be contacted by telephone 3 and 6 months after discharge regarding any SAEs and to confirm survival, as feasible ([Table 3](#)).

### **4.16.5. Review of Adverse Events**

The Investigator or qualified designee will assess each patient to evaluate for potential new or worsening AEs as specified in [Table 3](#). AEs will be graded and recorded according to National Cancer Institute Common Terminology Criteria for Adverse Events (NCI-CTCAE) version 5.0. Toxicities will be characterized in terms that include seriousness, causality, toxicity grading, and action taken with regards to study drug (see [Section 8.1.1](#))

Any AE/SAE while on study will be reported as outlined in [Section 8.1.5](#). Certain events should also be reported to the Sponsor as adverse events of special interest (AESIs); the definition of AESI is provided in [Section 8.1.3](#).

#### **4.16.5.1. Physical Examination, Vital Signs, Electrocardiograms, and Imaging**

Please refer to [Table 3](#).

### **4.16.6. Efficacy Assessments**

Efficacy will be assessed with the following parameters:

- Intubation/continuation/discontinuation of intubation/mechanical ventilation
- Supportive oxygenation interventions
- Baseline and every 12 hours as feasible: C-reactive protein, D-dimers, ferritin, IL-1, IL-6 to assess CRS evolution
- Mortality

- Decrease in viral burden from upper respiratory tract samples collected sequentially under treatment
- Persistence of allogeneic iNKT cells
- Baseline and every 24 hours as feasible: complete blood count with differential, comprehensive metabolic panel, procalcitonin, B-type natriuretic peptide, fibrinogen, prothrombin time, partial thromboplastin time, magnesium, angiotensin II level
- Available image (X-ray, CT-scans) to evaluate respiratory involvement (ARDS)
- Change in lung fitness through assessment of respiratory function
- Time from dosing to viral clearance
- Prevention of secondary infections

#### **4.16.7. Pharmacokinetics, Immunogenicity, and Pharmacogenomics Assessments**

Peripheral blood mononuclear cell samples for agenT-797 persistence and immunogenicity assessments will be collected for all patients at the timepoints described in [Table 3](#). The Sponsor may conduct research on DNA (blood and bronchial) specimens collected during this trial (pharmacogenomics).

